### Randomization

The 14 sites (8 in Connecticut and 6 in Delaware) selected for the study will be randomized into the 2 study arms, yielding 7 sites per condition, balanced by state. A research team member will use SAS 9.3 software to generate the allocation sequence assigning sites to condition. The software will generate randomized lists blocked by state, ensuring three experimental sites and three control sites in Delaware and four experimental sites and four control sites in Connecticut. The responsible team member will be blinded to site-specific information during randomization. Blinding is not possible, given the circumstances of the intervention.

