### Measurement

The intervention will be conducted over a period of 12 months and will be staggered across experimental sites. Organizational factors and PCCP competency will be measured by surveys of the leaders, clinical supervisors and direct care staff because reliable assessment requires multiple perspectives [30]. These surveys will be administered at baseline, 6 months and 12 months. Chart reviews will also be used to measure PCCP competency. Service engagement and consumer outcomes will be measured using state mental health data and Medicaid claims data.

Online assessment measures will be administered to all study participants, regardless of treatment condition. Researchers will collaborate with each CMHC to identify the leadership staff, clinical supervisors and direct care staff. An e-mail with an embedded URL linking participants to the online consent form and survey will be sent to each provider individually. Depending on their role in the agency, staff will receive one of the three surveys for direct care staff, clinical supervisors or executive leadership. The surveys are substantively equal with variation in the measurement versions and included language. Surveys will be completed at three time points: baseline, the midpoint of the intervention period (6 months) and postintervention (12 months). Each research site in the control condition will be paired with a site in the experimental condition, and the surveys will be e-mailed to pairs 1 month prior to the experimental site’s receipt of the PCCP intervention. Chart reviews will assess 75 service plans per site before and after the intervention.

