##### Person-centered care planning Documentation Quality Review Tool

This tool lists ten key indicators of person-centered care values and principles that can be applied to clinical record documentation. The measure generates a score from 0 to 10 (yes-or-no answers to ten indicators), with a higher score reflecting more person-centeredness. The PCCP Documentation Quality Review Tool was developed by the investigators in collaboration with the New York Association of Psychiatric Rehabilitation Services. This is not a validated measure, but an initial pilot administration of the tool in one large New York CMHC was positively received by the agency administration, both for its breadth of content and for its ease of administration.

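### The unqualified statement that blinding is impossible also covers chart reviewers, to whom its stated reason does not apply, so the between-arm chart-review comparison has no protection against knowledge of arm

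*Protocol article*

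**What the plan says.** Under Randomization, the protocol article states: "Blinding is not possible, given the circumstances of the intervention". The only masking it describes is that of the person who generates the allocation: "The responsible team member will be blinded to site-specific information during randomization". That protects the assignment of sites and has no bearing on outcome assessment.

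On chart review, the Measurement section says "Chart reviews will also be used to measure PCCP competency" and "Chart reviews will assess 75 service plans per site before and after the intervention". The section on the Documentation Quality Review Tool says "This tool lists ten key indicators of person-centered care values and principles that can be applied to clinical record documentation", and on scoring, "The measure generates a score from 0 to 10 (yes-or-no answers to ten indicators), with a higher score reflecting more person-centeredness". The tool "was developed by the investigators in collaboration with the New York Association of Psychiatric Rehabilitation Services", and the article adds: "This is not a validated measure".

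The Quantitative Data analysis section lists chart reviews among the outcome sources that each get a separate model. No section mentions masked or independent chart reviewers. The limitations in the Discussion do not mention unmasked rating.

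**The concern.** The reason given for not blinding is the intervention itself, that is, training and technical assistance delivered to known sites and staff. Those people cannot be masked. A chart reviewer reads a document. The site name, state, staff names and dates can be removed from it, and plans from both arms can be mixed. For this one outcome the sentence rules out a protection that is available.

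The outcome is also one that expectation could move. Each indicator is a yes/no judgement about values and principles, made on an unvalidated instrument built by the investigators. A reviewer who knows that a plan comes from an experimental site may credit a borderline item more readily. Such a shift would favour PCCP. Reviewing more charts would not remove it: a larger sample narrows the confidence interval around the biased value.

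**Working it through.** **Step 1: does the stated reason apply to each source of outcome data?**

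- Staff surveys: respondents know whether their site was trained. Masking is not possible, and the statement is correct.
- Medicaid claims and state data: these do not depend on study raters, so the question does not arise.
- Chart review: a rater judges written documentation. Masking to site, and therefore to arm, is feasible at least in part. The statement is wrong here.

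The point is therefore confined to chart review.

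**Step 2: which analysis is exposed?** The aim 2 competency analysis is restricted to agencies that received the intervention. It has no between-arm contrast for differential crediting to bias. What remains is the separate between-arm model for chart reviews in the Quantitative Data analysis section.

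**Step 3: how large a rating shift would matter? (illustration only)** The article gives no effect size or SD for the chart score, so it has no figure of its own to reproduce on this point.

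Inputs from the article:
- m = 75 plans per site (Measurement)
- 7 sites per arm (Randomization)
- ICC = 0.013 (Participants; the outcome it belongs to is not named)
- α = 0.05 and 80% power (Participants)

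Assumptions: two-sided test, a simple comparison of arms at follow-up, no covariate adjustment.

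- Design effect = 1 + (75 − 1) × 0.013 = 1.962
- Plans per arm = 7 × 75 = 525; effective number = 525 / 1.962 ≈ 268
- Standard error of the difference = √(2 × 1.962 / 525) ≈ 0.0865 SD
- Detectable difference, normal multiplier 2.80: 2.80 × 0.0865 ≈ 0.24 SD
- Detectable difference, t multiplier about 3.05 on 14 − 2 = 12 degrees of freedom: 3.05 × 0.0865 ≈ 0.26 SD

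If there is no true effect and unmasked rating adds an assumed shift to the experimental arm, the probability of a significant result is:

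| Assumed shift (SD) | t on 12 df | Normal |
|---|---|---|
| 0 | 5% | 5% |
| 0.05 | 8% | 9% |
| 0.10 | 19% | 21% |
| 0.20 | 57% | 64% |
| 0.30 | 89% | 93% |

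On the 0 to 10 scale, take an assumed SD of 1 to 2 points. The detectable difference of 0.24 SD is then 0.24 to 0.48 points. One extra indicator credited in one of four follow-up experimental charts, also an assumption, adds 0.25 × 1 = 0.25 points, which is about half to all of that difference.

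**The case against.** The strongest reply is that unmasked scoring is an inference. The sentence stands under Randomization, directly after the one on the person generating the allocation, and can be read as being about sites and providers only. The parts that describe chart review do not mention blinding. A condensed article may leave the identity of reviewers and the handling of records to a fuller document. Part of this stands. A reader might infer that charts will be scored with arm and time point known, but the article does not say so, and for time point the inference is weaker still. What does not stand is the defence by omission: the article makes a categorical statement with a reason attached, and that reason is false for this outcome.

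A second reply concerns importance. A reader might take the chart score to be the only competency measure that is not self-report by trained respondents, or the main check on competency. The article supports neither. The PCCQ has an administrative version, and respondents may rate staff processes instead of their own. Leaders and control-arm staff are surveyed without being trained. The triangulation that the article names for implementation outcomes is qualitative. Aim 1 rests on service engagement and clinical outcomes from claims and state data, which this point does not touch.

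Third, the bias size and the SD are assumptions, and the ICC is a pilot value that may not apply to chart scores. A larger ICC would widen the standard error and make any given shift weigh less. This is accepted: the table shows sensitivity and is not evidence of bias in this trial.

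Finally, the training aims at how plans are written, and the tool scores that content, so wording may reveal the arm. That limits masking. It does not remove the value of taking out site and date, which are certain cues.

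**Conclusion.** The concern holds for the between-arm chart-review model and no further. The sentence on blinding is too broad: its reason covers sites, staff and trainers, and it leaves a rater-judged outcome on an unvalidated, investigator-developed tool without protection against knowledge of arm. The size of any bias cannot be known from the article. On the illustrative inputs the model could detect about 0.24 to 0.26 SD, so a differential rating shift of 0.10 to 0.20 SD would be enough to raise the false-positive rate from 5% to somewhere between about 19% and 64%. This rests on the stated ICC applying to chart scores and on assumed shifts. It is a correctable weakness in one outcome and does not undermine the trial's engagement and clinical results.

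**What to change.** 1. Limit the sentence under Randomization to sites, staff and trainers.
2. State in the Measurement section that charts are scored by the existing chart reviewers and not by those who deliver the training. Site, state, staff names and dates are removed, and plans are scored under study codes, in random order, with the arms mixed and, where feasible, the periods mixed too.
3. If this cannot be done, list unmasked chart rating among the limitations in the Discussion.

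The cost is redaction and coding. If 75 plans are reviewed at each of two periods, that is 14 × 75 × 2 = 2,100 plans. Mixing periods also means holding baseline plans until follow-up plans exist, across sites with staggered starts. The Trial status section says that baseline data collection and training have begun; if the service plans are retained as records, they can still be coded and scored later. Masking will be incomplete where the wording of a plan shows the training, and the report should say so.

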### Intervention

PCCP provides a framework for the collaborative cocreation of a recovery-oriented treatment plan that is driven by an individual’s most valued life goals. Providers will learn how to elicit and empathize with their client’s subjective experiences as a whole person and how to help the consumer identify and articulate interests, preferences and personal recovery goals. Challenges include reframing symptoms and impairments as barriers to goal attainment; reframing the use of medications as tools for overcoming these barriers and moving ahead in one’s life; instilling hope and encouraging the person’s incremental efforts in the face of fear, uncertainty and demoralization; identifying short-term, realistic and measurable objectives that can be achieved within the plan period of 3 to 6 months while keeping these objectives explicitly connected to longer-term aspirations that might span years; and expanding a person’s network to include natural supporters as well as professional care providers.

The PCCP implementation strategy targets change in direct service provider behavior by providing training and follow-up TA to clinical supervisors and nominated direct care staff over a yearlong period. This targeted staff selection is aimed at contributing strategies for scaling up and sustaining practices in large mental health systems. This strategy serves to integrate ongoing, knowledgeable supervision of direct care staff from onset. Additionally, the nominated direct care staff are selected in part for their demonstrated leadership potential. Clinical supervisors and direct care staff will employ this interpersonal influence and formal and informal leadership roles as “change agents” within their teams and programs [35,36].

To ensure rigorous testing, this implementation-as-usual strategy will follow the current “gold standard” for training in EBP. This includes a workshop with behavioral rehearsal (that is, practice), ongoing supervision and coaching on skills, and a provider training manual to reinforce learning [37,38]. Clinical supervisors and direct care staff will receive 2-day training aimed at providing practical, nuts-and-bolts guidance for how to maintain a strengths-based recovery orientation within a comprehensive, person-centered plan that also meets rigorous documentation standards. The training will address how to provide PCCP and how to transfer this knowledge and skills via supervision to direct services staff. It begins with a brief introduction to the broader construct of recovery-oriented care to ensure that participants have a shared conceptual foundation for the more advanced PCCP skills training. The content of PCCP training is organized around a published logic model [11] that walks supervisors through a series of steps in creating person-centered recovery plans. These steps include initial request for services, comprehensive strengths-based assessment, shared prioritization of action areas, collaborative development of recovery plan content (including goals, strengths and/or barriers, and short-term objectives), delivery of services consistent with an established plan, and monitoring of both the quality of the planning process and its impact on consumer outcomes. In each of these areas, opportunities to maximize the person-centered nature of both the process (that is, how roles, relationships and planning meetings look different in PCCP) and the documentation (that is, the resultant written recovery plan) are highlighted. Significant emphasis is placed on the changing roles of both the consumer and the practitioner in PCCP, with tools provided to support the development of competence and confidence in these shifting roles.

Trainees will be given the provider training manual as well as a consumer toolkit*.* The provider manual is a published 154-page guide developed by the Yale Program for Recovery and Community Health. The consumer toolkit, also developed by Yale Program for Recovery and Community Health, is a 24-page guide designed to explain to consumers the process of person-centered care planning. Designed for administrators and providers, the manual gives detailed step-by-step guidance on how to write person-centered plans for people receiving behavioral health plans. To strengthen the transfer of learning from the initial training to participants’ daily work, clinical supervisors will be asked to participate in two follow-up TA telephone calls per month. The first call of each month will be a case presentation and consultation call. The supervisor’s team will be invited to participate in the call, and training consultants will offer live modeling of how supervisors should conduct these PCCP feedback sessions with their supervisees. The second monthly call will involve the clinical supervisors only and will be fully dedicated to supporting supervisors with implementation issues they encounter as they encourage the adoption of PCCP by their team members. The training team will keep logs of the training and record process notes of TA calls to measure the frequency and intensity of training given to each provider.

### Measurement

The intervention will be conducted over a period of 12 months and will be staggered across experimental sites. Organizational factors and PCCP competency will be measured by surveys of the leaders, clinical supervisors and direct care staff because reliable assessment requires multiple perspectives [30]. These surveys will be administered at baseline, 6 months and 12 months. Chart reviews will also be used to measure PCCP competency. Service engagement and consumer outcomes will be measured using state mental health data and Medicaid claims data.

Online assessment measures will be administered to all study participants, regardless of treatment condition. Researchers will collaborate with each CMHC to identify the leadership staff, clinical supervisors and direct care staff. An e-mail with an embedded URL linking participants to the online consent form and survey will be sent to each provider individually. Depending on their role in the agency, staff will receive one of the three surveys for direct care staff, clinical supervisors or executive leadership. The surveys are substantively equal with variation in the measurement versions and included language. Surveys will be completed at three time points: baseline, the midpoint of the intervention period (6 months) and postintervention (12 months). Each research site in the control condition will be paired with a site in the experimental condition, and the surveys will be e-mailed to pairs 1 month prior to the experimental site’s receipt of the PCCP intervention. Chart reviews will assess 75 service plans per site before and after the intervention.

#### Person-centered care planning competency

##### Person-Centered Care Questionnaire, administrative and provider versions

The Person-Centered Care Questionnaire (PCCQ), created in 2009 by [name] and [name] of the Yale Program for Recovery and Community Health, is a 32-item measure designed to assess the degree to which service planning is person-centered, with higher scores associated with a more person-centered service plan. This measure has not been validated. The PCCQ has been used to measure intervention fidelity by the investigative team in their work with multiple states. Respondents rate either their service-planning processes or the staff processes on a 5-point scale ranging from “strongly disagree” to “strongly agree”.

##### Person-centered care planning Documentation Quality Review Tool

This tool lists ten key indicators of person-centered care values and principles that can be applied to clinical record documentation. The measure generates a score from 0 to 10 (yes-or-no answers to ten indicators), with a higher score reflecting more person-centeredness. The PCCP Documentation Quality Review Tool was developed by the investigators in collaboration with the New York Association of Psychiatric Rehabilitation Services. This is not a validated measure, but an initial pilot administration of the tool in one large New York CMHC was positively received by the agency administration, both for its breadth of content and for its ease of administration.

#### Organizational factors

##### Multifactor Leadership Questionnaire, leader and rater (staff) versions

The Multifactor Leadership Questionnaire 5x-Short Form [39] is a widely used measure of leadership in organizations, and its dimensions have been associated with organizational performance and success [22]. This study focused on transformational leadership, which is composed of five subscales: idealized influence (belief of leadership character; α = 0.91), idealized influence (observed leadership behavior; α = 0.86), inspirational motivation (α = 0.94), intellectual stimulation (α = 0.93) and individual consideration (α = 0.87) [25]. Clinical supervisory and direct care staff were asked to rate the executive leadership, and the executive leadership were asked to rate themselves, on a 5-point frequency scale ranging from “not at all” to “frequently, if not always”, with higher ratings indicating a higher degree of idealized influence, inspiration, intellectual stimulation and individual consideration.

##### Organizational Readiness for Change Scale, director and staff versions

The Organizational Readiness for Change Scale [30] is used to assess provider perceptions of the readiness for change. This self-administered measure has four domains: motivational factors, staff attributes, program resources and organizational climate. This study focuses on the 30-item organizational climate domain with six subscales that correspond to organizational features associated with implementation of innovative practices [40,41]. The selected subscales include mission, cohesion, autonomy, communication, stress and change. Each subscale has acceptable internal consistency values ranging from 0.76 to 0.82 [30]. Respondents are asked to rate the working environment at their agency on a 5-point scale ranging from “strongly disagree” to “strongly agree”, with higher ratings indicating higher degrees of climate for change.

##### Recovery Self-Assessment–Revised, administrator and provider versions

The Recovery Self-Assessment–Revised scale (RSA) [42] is a 36-item measure assessing the degree to which recovery-oriented practices are implemented in an agency. Respondents are asked to rate the agency as a whole on a 5-point scale ranging from “strongly disagree” to “strongly agree” with items related to the scale’s five components: life goals, involvement, diversity of treatment options, choice and individually tailored services. Higher scores indicate a higher integration of recovery-oriented practices. The RSA has been used as a quality improvement and/or research tool in over 35 states and in several different countries. In previous research, the RSA has been demonstrated to have excellent internal consistency, reliability and validity [42-44].

#### Consumer outcomes

##### Community mental health visits

Mental health visits at each agency are reported via the CMHC Service Ticket Form, which is completed by providers after each scheduled appointment or unscheduled visit. Visits are coded as no show, canceled, unscheduled or scheduled.

##### Outpatient mental health service use

Medicaid claims data will be used to measure use of medication management, case management, individual and group psychotherapy services, and rehabilitative services. Relevant claims will be identified based on presence of an International Classification of Diseases, Ninth Revision, Clinical Modification (ICD-9-CM), mental health diagnostic code as primary diagnoses on evaluation and management visit claims or by corresponding Current Procedural Terminology (CPT) codes in all outpatient settings except emergency departments.

##### Medication adherence

Medicaid claims data will be used to measure adherence to psychiatric medications. We will calculate adherence to newly initiated and ongoing use of antidepressants, antipsychotics and mood stabilizers using the medication possession ratio (MPR) [45]. The MPR is a continuous measure of the usable days supplied from all prescriptions in each period divided by the number of days in each period.

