Each supervisor will nominate two direct care staff who report to them. They will nominate individuals based on whether they fulfill the criteria of change agents, which are that they have worked at the agency for more than 1 year, have demonstrated leadership potential, are open to change and adoption of new practices and are perceived as a resource and/or role model by other direct care staff.

Secondary data will be used to assess consumer outcomes. Consumers eligible for this study will be adults who have received services at the CMHCs continuously for 1 year prior to the study. We will use the Medicaid and state mental health data of all eligible consumers.

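### The medication possession ratio uses all days in the period as denominator for newly started drugs too, so a new user's score depends on start date as well as adherence

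*Protocol article*

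**What the plan says.** Under Measurement, Medication adherence, the protocol article states: "We will calculate adherence to newly initiated and ongoing use of antidepressants, antipsychotics and mood stabilizers using the medication possession ratio". The next sentence defines the MPR as a continuous measure of the "usable days supplied from all prescriptions in each period divided by the number of days in each period". No other denominator is given for a drug first filled inside a period, and the word period is not defined.

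On the population, Methods, Participants says: "Consumers eligible for this study will be adults who have received services at the CMHCs continuously for 1 year prior to the study". It adds: "We will use the Medicaid and state mental health data of all eligible consumers". Eligibility therefore does not require earlier use of the drug class.

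Under Quantitative data analysis, each Aim 1 outcome is compared between arms in a linear mixed model. The primary test is at 24 months, and a growth curve runs over baseline, 12 and 24 months with its focus on the time-by-treatment interaction. The listed covariates are baseline consumer factors; neither new-start status nor start date is among them.

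**The concern.** The two consecutive sentences on adherence state a rule, and the rule treats two kinds of use alike. For ongoing use, dividing by all days in the period is natural, because the consumer could have held supply on any of those days. For a drug started partway through, the days before the first fill are not days of non-adherence, yet the formula counts them as such. The score then mixes when the drug was started with how well it was taken.

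This matters for the comparison because initiation may itself respond to the intervention. The Intervention section describes training staff to present medicines as a means of getting past obstacles to personal goals, and the Outcomes part of the conceptual framework treats the decision to use medication as something choice can influence. A difference in initiation that arises after randomization would enter the adherence outcome as an apparent difference in adherence. Baseline covariates cannot remove it.

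**Working it through.** The protocol gives no expected mean, standard deviation, effect size or new-start share for the MPR, so there is no figure to reproduce. The check is arithmetic on the stated definition.

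**Inputs from the protocol.** Numerator: usable days supplied in the period. Denominator: days in the period. Measures at baseline, 12 and 24 months.

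**Assumed inputs.** Period length P = 365 days; new starts spread evenly over the period; true adherence *a* the same in new and ongoing users; a share *p* of the analysed users who are new starters.

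**One fully adherent new user.** If *d* days pass before the first fill, MPR = (P − d)/P.

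| First fill on day | Calculation | MPR |
|---|---|---|
| 1 | 365/365 | 1.00 |
| 92 | 274/365 | 0.75 |
| 183 | 183/365 | 0.50 |
| 275 | 91/365 | 0.25 |
| 336 | 30/365 | 0.08 |

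The mean over evenly spread start days is (P + 1)/(2P) = 366/730 = 0.501. A period of 182 days gives the same pattern (mean 0.503).

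**Arm means, users only.** Mean MPR = (1 − p)a + p(0.5a). A between-arm difference Δp in the share of new starters therefore shifts the mean by −0.5aΔp with no difference in true adherence.

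| True adherence *a* | Δp = 0.05 | Δp = 0.10 | Δp = 0.20 |
|---|---|---|---|
| 0.75 | −0.019 | −0.0375 | −0.075 |
| 0.80 | −0.020 | −0.040 | −0.080 |
| 1.00 | −0.025 | −0.050 | −0.100 |

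With equal shares the arm difference is 0, but both means are too low: at a = 1.0 and p = 0.20, each arm shows 0.80 + 0.20 × 0.5 = 0.90.

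**Arm means, non-users scored 0.** A consumer who starts moves from 0 to 0.5a on average, which is 0.375 at a = 0.75. Ten points more starters among all consumers then raise the mean by 0.10 × 0.375 = 0.0375. The sign is the reverse of the users-only case.

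**Time course.** With 12-month periods, a consumer who starts in year 1 and continues at a = 0.75 scores 0.375 on average at 12 months and 0.75 at 24 months. This is an apparent rise of 0.375 with no change in adherence. A year-2 starter is scored low at 24 months. Unequal starts by arm can therefore move the time-by-treatment slope, upwards or downwards depending on when the starts fall and on whether new users have a baseline value.

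**With the denominator counted from first fill.** A fully adherent new user scores 1.00 whatever the start date, and the arm difference caused by unequal shares is 0 under the assumption of equal *a*.

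**The case against.** The strongest reply is that period is undefined. If it ran for each person from the first fill, the problem would vanish. Naming new and ongoing use as two kinds is also compatible with calculating them separately. This is fair, but the text does not say either, and repeated measures at baseline, 12 and 24 months read naturally as periods common to everyone.

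Second, a reader might infer that more new starts would always look like worse adherence. The protocol does not support that. It does not say whether consumers without any fill are left out or scored 0, and the intent-to-treat statement together with the use of data on all eligible consumers leaves the second possibility open. If drug classes are pooled, a current user who switches or adds a drug need not lose days at all.

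Third, a reader might take the bias to differ by arm as a matter of fact. It does so only if the share or timing of starts differs. The protocol gives a plausible route for that but predicts no such difference.

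Fourth, exposure at the primary time point is limited. Under 12-month periods, a drug started in year 1 has a full denominator in year 2.

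Fifth, a reader might infer that inpatient days and days without Medicaid coverage are wrongly kept in the denominator, or that the ratio may exceed 1. The article is silent on these points. They are claims-programming rules that a condensed article commonly leaves to the full plan, so they are not shown to be mishandled.

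The second to fifth points narrow the concern. None of them repairs the denominator for new starts.

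**Conclusion.** The point stands in limited form. As written, and read with common study periods, the MPR understates adherence for anyone who starts a drug inside the period: on average a fully adherent starter is recorded at about half. Whether this biases the arm comparison depends on new starts differing by arm in share or timing, and the sign depends on how non-users are handled.

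In a users-only analysis with true adherence of 0.75, evenly spread starts and 12-month periods, a 5 to 10 point excess of new starters lowers the mean MPR by about 0.02 to 0.04. All of these inputs are assumptions. The 24-month test is then exposed only to year-2 starts; the 12-month test and the growth curve are exposed to year-1 starts as well. Medication adherence is one of several consumer outcomes, so this is a definition to put right and not a threat to the whole trial.

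**What to change.** For newly initiated drugs, count the denominator from the first fill to the end of the period, and set a minimum follow-up or a weight for late starters. Keep all days in the period for ongoing use. Define period explicitly, and state whether consumers with no fill are excluded or scored 0, since this settles the direction of any remaining effect.

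Analyse new and ongoing users separately. The new denominator removes the start-date artefact, but if new users truly adhere differently, a pooled mean would still move with their share. New-user status after baseline arises after randomization, so that comparison needs cautious interpretation.

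The change uses the same claims and amounts to a revised definition in the claims program, to be fixed before outcomes are analysed. The downside is small: late starters contribute shorter and noisier observation.

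As a secondary refinement, inpatient and uncovered days can be taken out of the denominator using the claims data. Length of stay for psychiatric hospitalizations is already to be coded.
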